### Control condition

After inpatient treatment, the patients in the CG will receive treatment as usual with routine care that does not involve the aftercare coordination by phone that the patients in the intervention group will receive. The patients in the control group will not have any contact with their therapists from the clinic after the inpatient treatment.

### Outcome assessment

#### Primary outcome measures

The primary outcome measure is symptom severity, which will be assessed using Beck's Depression Inventory (BDI-II) [19]. The BDI-II consists of 21 items that are rated on a four-point Likert scale and yields a total score via the summation of the ratings for the individual items (range: 0 to 63; higher scores indicate higher symptom severity). The mean BDI cut-off scores for minimal, mild, moderate and severe depressive symptoms are 7.7, 19.1, 27.4 and 33.0, respectively. The BDI-II is a reliable and valid measure of depression symptoms with an internal consistency ranging from .92 to .93. This instrument has been widely used and is sensitive to change.

#### Secondary outcome measures

The secondary outcomes include health-related quality of life as measured with the EuroQol-5D [20] and the Short Form 8 Health Survey (SF8) [21]. The >EuroQol-5D is a generic instrument that measures health-related

quality of life in five dimensions; i.e., mobility, self-care, usual activities, pain/discomfort and anxiety/depression. Health-related quality of life will also be assessed with a visual analogue scale (range: 0 to 100; higher ratings indicate higher quality of life). The SF-8 is a short version of the SF-36 [22] allows for the calculation of scores for physical and mental health (range: 0 to 100; higher scores indicate better statuses). This instrument has good psychometric properties with an internal consistency between .70 and .88 [23].

As an additional secondary outcome, the proportion of patients who managed to organize outpatient psychotherapy at follow-up will be assessed with self-report items. Whether self-efficacy can be improved by the case management-based intervention that aims to empowering the patients to become active will also be investigated. The German General Self-Efficacy Scale (SWE) [24] will be used to assess self-efficacy. This scale comprises 10 four-point Likert-scale items that range from 1 ('totally disagree') to 4 ('totally agree'). The questionnaire includes items such as "If there are challenges, I can find a way to succeed" and "I can find a solution for every problem". The summed scores range between 10 and 40, and higher scores indicate greater general self-efficacy. The internal consistency of this instrument ranges from .80 to .90 [24].

### Additional measures

To investigate whether patient characteristics can predict the outcomes of aftercare coordination, the following demographic and clinical characteristics will be collected via a self-report questionnaire: age, gender, marital status and partnership, children, level of education, employment status and occupational situation, and medical and psychosocial treatment prior to the inpatient treatment. To examine whether the therapeutic alliance is associated with the primary outcome, the therapeutic relationship will be measured with the Helping Alliance Questionnaire (HAQ-S) [25], which consists of 11 items that are rated on a six-point Likert scale ranging from -3 ('strongly disagree') to 3 ('strongly agree'). A total score is calculated, and higher total scores are indicative of better alliances. Research has demonstrated the good reliability and validity of this instrument [26].

### Anxiety-specific measures

Additionally, Beck's Anxiety Inventory (BAI) [27] will be utilized to measure the changes in anxiety symptom severity. The BAI contains 21 items that assess the degree to which the respondent has been affected by physical or cognitive symptoms of anxiety during the past week. The BAI items are also meant to reflect panic attack symptoms. The total score ranges from 0 to 63, and high scores indicate more severe anxiety. The internal consistency ranges from .83 to .95. To gather data regarding changes in the severity

of the symptoms of specific anxiety disorders, the following diagnosis-specific outcome measures will be used only in the questionnaires for the patients with anxiety diagnoses. Generalized anxiety disorder symptoms will be assessed with the seven-item Generalized Anxiety Disorder Scale (GAD-7) [28], which measures the symptom severity over the previous two weeks on a four-point Likert scale that ranges from 0 (“not at all”) to 3 (“nearly every day”). The sum score ranges from 0 to 21. Scores of 5, 10, and 15 represent the cut-off points for mild, moderate and severe anxiety, respectively. This instrument is a reliable and valid measure of anxiety with an internal consistency of .89 [29]. Panic disorder symptoms will be measured with the Body Sensations Questionnaire (BSQ) and the Agoraphobic Cognitions Questionnaire (ACQ) [30]. The BSQ contains 17 items concerning the degree to which the patient fear somatic symptoms that are commonly associated with anxiety and panic attacks. This inventory assesses the fear of certain body sensations. The items are rated on a five-point Likert scale ranging from 1 = “not frightened or worried by this sensation” to 5 = “extremely frightened by this sensation”. The total score is calculated by averaging the individual item ratings. The internal consistencies in different samples range from .80 to .95 [31]. The ACQ measures the frequency of fear-related cognitions, and the fear of negative social or health consequences of fear. The ACQ contains 14 items (6 behavioral-social and 8 physical items) that are rated on a five-point Likert scale ranging from 1 = “the thought never occurs” to 5 = “the thought always occurs when I am nervous”. The internal consistency in different samples ranges from .74 to .87 [31]. The total score is derived by averaging the individual item ratings.

Agoraphobic symptoms will be assessed with the Mobility Inventory (MI) [32], which is a 26-item self-report questionnaire that was designed to assess the severity of the avoidance of common agoraphobic situations. Each situation is rated on a five-point Likert scale ranging from 0 (never avoids) to 4 (always avoids). Each situation is rated twice to reflect the degrees to which each situation is avoided by the agoraphobic participant when he is alone and when he is accompanied. The MI is scored by calculating the average avoidance rating across all situations for the Avoidance Alone and Avoidance Accompanied Scales. The internal consistency in different samples ranges from .85 to .97 [31].

The Social Phobia Scale (SPS) and the Social Interaction Anxiety Scale (SIAS) [33] will be used to measure social anxiety. The SPS assesses anxiety in 20 performance situations, and the SIAS was constructed to measure anxiety in 20 social interaction situations. Each situation is rated on a 4-point scale ranging from 0 to 4. The sum scores for both questionnaires range from 0 to 80, and higher scores

represent greater anxiety about being observed by others or social interactional anxiety. The cut-offs are >24 for the SPS and >35 for the SIAS. The internal consistencies in different German samples range from .94 to .95 for the SPS and .86 to .88 for the SIAS [34].

### Process measurements

To identify the main contents and to determine if the patients benefit during the course of the aftercare coordination from the perspective of the therapists, a process evaluation will be conducted. After every phone contact, the therapist will answer questions such as ‘Which steps have been generated, and did the patient carry out these steps?’, ‘Is the patient motivated and open to the aftercare coordination and benefiting from it?’ and ‘What was the central task of the therapist during the phone contact, e.g., motivating the patient, informing and consulting, planning the next steps, and controlling and monitoring of the patient’s progress?’ in the developed questionnaire.

Furthermore the patients’ satisfaction with the intervention procedures and acceptance of the aftercare coordination will be assessed with 25 self-generated items. For example, the items will include “The phone contacts helped me in finding my way back to everyday life” and “My therapist and I always discussed the individual steps of my aftercare support” and will be rated on a five-point Likert scale ranging from 1 (‘totally agree’) to 5 (‘totally disagree’). Additionally, the patients will be asked to answer some open questions such as “What could be improved regarding the aftercare coordination?”.

### Statistical analyses

The primary analysis will focus on the changes in symptom severity from  $t_1$  to  $t_3$  as assessed with the BDI-II. Comparisons between the IG and the CG will be calculated with mixed model analyses of covariance (ANCOVAs) with symptom severity as the dependent variable and gender and initial symptom severity as covariates. An advantage of this method is that it includes all available data even if the data from another time point for a specific person are missing. Other secondary analyses will be performed regarding changes in health-related quality of life, self-efficacy and anxiety symptom severity from  $t_1$  to  $t_2$  and from  $t_1$  to  $t_3$ . Following the intention-to-treat approach (ITT), we will analyze all randomized participants in the primary analysis to avoid biases such as non-random attrition of the participants. Additionally, a sensitivity analysis following the per-protocol approach will be conducted. This analysis will be performed including only the participants that have completed all measurements. To investigate whether the patient characteristics (e.g., age, level of education, and psychosocial treatment before the inpatient treatment) and patient ratings of the therapeutic alliance predict the outcomes

of the aftercare coordination, different regression analysis models will be applied to the primary and secondary outcomes. Process evaluation and data about the patients' satisfaction and acceptance will be investigated via descriptive and qualitative analyses. We will also conduct drop-out analyses to compare the demographic and clinical baseline characteristics of the completers and non-completers ( $t$ - and  $\chi^2$ -tests). The analyses will be conducted with SPSS 21.

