### Recruitment and data collection

The patients who fulfill the study inclusion criteria will be recruited consecutively by their therapists at the beginning of their inpatient treatment in the four cooperating psychotherapeutic inpatient units (St. Franziska-Stift Bad Kreuznach, MediClin Seepark Klinik Bad Bodenteich, Segeberger Kliniken Gruppe Bad Segeberg and Luisenlinik Bad Dürreheim). Prior to participation, the patients will be informed with oral and written information regarding the study by their therapists. After written informed consent is obtained, the patients will be randomly assigned to the IG or the CG.

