#### Randomization

The patients will be randomized using a stratified block randomization with randomly varying block size to ensure concealment and equal group sizes, and the randomization will be stratified by the participating clinical units. The randomization will take place at the individual level at the University Medical Center Hamburg-Eppendorf one week before the beginning of the intervention. The allocation schedule was created with a computer program (Microsoft Excel, Windows) by a researcher at the University Medical Center Hamburg-Eppendorf. The therapists will be informed about the randomization outcome prior to the last psychotherapeutic session during inpatient treatment so that they can inform the patients about their group assignment before discharge.

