#### Power calculation

We expect a moderate effect size, which is defined as  $f = 0.25$  according to Cohen [35], for the primary outcome because recent studies that have investigated aftercare programs have reported moderate effect sizes in terms of changes in symptom severity (e.g., depressiveness) [36]. We expect a reduction of the error variance of approximately 30% due to the inclusion of initial symptom severity (BDI at  $t_1$ ) as a covariate (which can be expected to be uncorrelated with the study conditions due to the randomization). These considerations lead to an adjusted effect size of  $f = 0.29$ . To detect a moderate effect between the intervention and control groups in terms of the symptom severity with a power of 80% and an  $\alpha$  of 0.05, a sample size of  $N = 96$  (48 per group) is required. Based on an expected dropout rate of approximately 50% from baseline ( $t_1$ ) to 9 months of follow-up ( $t_3$ ), we aim to include a sample of  $N = 192$  (96 per group) to perform the per-protocol analysis with a sufficient sample size.

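### Randomization is stratified by clinic but the primary ANCOVA leaves clinic out, giving a slightly conservative test and a small, avoidable loss of precision

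*Protocol*

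**What the plan says.** Under Randomization, the protocol plans "stratified block randomization with randomly varying block size to ensure concealment and equal group sizes", and adds that "the randomization will be stratified by the participating clinical units". No other stratification factor is named. Recruitment takes place "in the four cooperating psychotherapeutic inpatient units", so there are four strata.

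Under Statistical analyses, the primary comparison of the two arms is a mixed-model ANCOVA "with symptom severity as the dependent variable and gender and initial symptom severity as covariates". The benefit claimed for the mixed model is that "it includes all available data even if the data from another time point for a specific person are missing", which concerns repeated measurements within a patient. Clinic does not appear as a fixed or a random effect anywhere in the document.

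Under Power calculation, the only variance reduction counted is a "reduction of the error variance of approximately 30% due to the inclusion of initial symptom severity". Clinic plays no part there either.

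**The concern.** When allocation is blocked within clinic, each clinic contributes nearly equal numbers to both arms. Differences between clinics in the nine-month BDI-II then largely cancel out of the arm comparison, and its true variance is smaller than under unrestricted randomization. An analysis without clinic does not register this. It counts the between-clinic variation as residual noise and reports a standard error that is too large.

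The plan thus adjusts for gender, which was not used in the randomization, and leaves out the factor that was. At stake are confidence intervals a little wider than they need be, a test a little below its nominal level, and some unused power in a design that aims at 80% with no margin beyond the dropout allowance. A clinic effect is conceivable on the protocol's own account: each unit's own therapists deliver the calls, and the Discussion says that success depends partly on structural conditions such as waiting times, which could vary by location.

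**Working it through.** **Inputs.** From Power calculation: f = 0.29 after baseline adjustment (taken as stated), 80% power, alpha 0.05, N = 96 analysable (48 per group), 50% dropout, 192 randomized. From Recruitment and Randomization: four clinics, blocks within clinic. Not in the documents: rho, the share of residual variance that lies between clinics after baseline adjustment. It is assumed here at 0%, 2%, 5% and 10%.

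**The plan's own figure.** Noncentral F test, 1 numerator df, noncentrality N × f² = 96 × 0.0841 = 8.07, two-sided alpha 0.05: power 80.3%, and 96 is the smallest N that reaches 80%. Sidedness is not stated, but a one-sided calculation gives 74 and does not match. Then 96 / (1 − 0.5) = 192. Both figures reproduce.

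**Fully balanced data, N = 96.** Total residual variance is held at the planned value.

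- Ratio of model SE to true SE without clinic: 1/√(1 − rho).
- True type I error without clinic: 2 × [1 − Φ(1.96/√(1 − rho))].
- Power without clinic: Φ((0.29 × √96 − 1.985)/√(1 − rho)), where 0.29 × √96 = 2.841.
- Power with clinic: noncentral F with f = 0.29/√(1 − rho) and 3 further df.

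| rho | SE too large by | True type I error | Power without clinic | Power with clinic |
|---|---|---|---|---|
| 0% | 0 | 5.0% | 80.4% | 80.3% |
| 2% | 1.0% | 4.8% | 80.7% | 81.0% |
| 5% | 2.6% | 4.4% | 81.0% | 82.2% |
| 10% | 5.4% | 3.9% | 81.7% | 84.2% |

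The 0.1-point difference in the first row comes from the normal approximation in the fourth column. At rho = 0, three extra df cost less than 0.1 power point.

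**Simulation, balanced data** (four clinics of 24, blocks of 4 or 6, 4000 runs per setting, outcome treated as already baseline-adjusted). At rho = 10% under the null, the model without clinic had a mean SE of 0.2045 against a true SD of 0.1972 and rejected in 4.3% of runs. With clinic the SE was 0.1939 against 0.1970, and rejection was 5.1%.

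**Allowing for the stated dropout.** Blocking balances the 192 randomized, not the 96 with t3 data. In a clinic with n patients split equally, random retention of half gives the difference in arm counts a variance of 2 × (n/2) × ½ × ½ = n/4. Unrestricted randomization of the n/2 retained patients would give n/2. So half of the between-clinic variance returns to the arm difference, and the SE ratio becomes 1/√(1 − rho/2):

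- rho 2%: SE 0.5% too large, type I error 4.9%
- rho 5%: SE 1.3% too large, type I error 4.7%
- rho 10%: SE 2.6% too large, type I error 4.4%

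Two simulations with 192 randomized and 50% random dropout at rho = 10% gave null rejection without clinic of 4.13% (4000 runs) and 4.45% (8000 runs). Pooled: (0.0413 × 4000 + 0.0445 × 8000)/12000 = 4.3%. Power without v with clinic was 81.9 v 84.1% and 80.9 v 82.9%. At rho = 5% it was 82.3 v 82.9% and 80.5 v 80.9%. At rho = 2% (8000 runs only) it was 79.9 v 79.4%. The differences at 2% and 5% are within or close to simulation error.

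**The case against.** The strongest case against acting has three parts.

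*The size is unknown and may be nil.* No section gives the between-clinic variance of the nine-month BDI-II, and baseline BDI-II, already in the model, absorbs clinic differences in initial severity. This stands. It is why the result is given as a range that starts at zero.

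*The error is on the safe side.* This also stands. From a mismatch between randomization and analysis a reader might infer a biased effect estimate, an inflated false-positive rate or an inadequate sample size. The documents support none of these. Individual randomization keeps the estimate unbiased, omitting a stratifier makes the test conservative, and 96 and 192 reproduce with or without clinic. A reader might also set the power with clinic against the planned 80.3% and infer a gain of up to 84.2 − 80.3 = 3.9 points. But 80.3% is the power when clinic explains nothing. At the same assumed clinic effect the gain is 84.2 − 81.7 = 2.5 points at most.

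*The full model may be in a statistical analysis plan.* The protocol does not say that its covariates are the only terms, and it does not list the random effects. But it names the primary covariates without deferring the choice, and it explains the mixed model solely by missing time points. As written, the stated primary model omits the stratifier, and that can be raised from the protocol alone.

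**Conclusion.** The mismatch is certain; its consequence is small and conservative. If clinic explains 2% to 10% of residual variance, the like-for-like power forgone is about 0.3 to 2.5 points with balanced data. The standard error is at most 1.0% to 5.4% too large with full balance and roughly half that under 50% dropout, where the true type I error is about 4.3 to 5% rather than 5%. With no clinic effect, nothing is lost.

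These figures rest on the assumed clinic share, equal-sized clinics in the simulations, dropout unrelated to arm or clinic, and a single t3 comparison standing in for the repeated-measures model. The point does not threaten the trial's conclusion. It is a minor improvement, worth making because it costs nothing.

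**What to change.** In Statistical analyses, add clinical unit as a four-level fixed effect to the primary mixed-model ANCOVA, alongside gender and baseline BDI-II. Do the same in the secondary between-group analyses and in the completers' sensitivity analysis. State it before outcome data are seen, so that it is not a post hoc change of model.

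The cost is one phrase and 3 degrees of freedom out of about 90. Clinic is already recorded for the randomization, so no new data are needed, and the sample size stays as planned.

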## Background

Depressive and anxiety disorders are among the most prevalent mental disorders and cause significant personal, social and economic burdens. Despite the high 12-month prevalence rates of 15.3% for anxiety and 7.7% for depression in Germany [1] only approximately half of these patients receive appropriate treatment [2]. This finding is indicative of undertreatment and the need for the optimization in the care of patients with anxiety and depression. Significant barriers in the patients' pathways include communication and coordination problems between different services or providers [3-6]. The aftercare following inpatient treatment represents one of these gaps. After inpatient treatment, follow-up outpatient psychotherapy is clinically indicated for the majority of patients with anxiety and depressive disorders [7]. Here, the aims are to consolidate the treatment outcomes and to minimize the so-called rebound-effect, i.e., the long-term reduction in positive treatment effects following inpatient treatment. Although there is evidence supporting the effectiveness of inpatient treatment, treatment effects often decrease after treatment. A portion of patients who exhibit improvements at termination relapse and continue to seek help from a variety of mental health providers [8]. Depressive disorders are particularly highly recurrent, and the risk of a further episode increases with each additional episode; thus, the prevention of relapse is extremely desirable [9]. It can be assumed that the therapeutic alliance represents a protective factor against rebound effect; numerous studies have found that the therapeutic alliance is relevant to the outcome of psychotherapy [10] and the prevention of relapse [11]. However, the high risk of relapse indicates that follow-up support, e.g., outpatient psychotherapy, is necessary for patients to maintain long-term treatment outcomes after returning to everyday life. In addition to outpatient psychotherapy and primary and specialist care, patients can also profit from low-intensity offerings such as self-help groups and counseling. Thus, several aftercare treatment options exist, but many patients do not access follow-up treatment. Treatment barriers that result from a lack of integration of the different steps in care can occur on the systemic level (e.g., long waiting times for outpatient psychotherapy) and on the individual level (e.g., insufficient patient awareness of available treatments) [6].

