#### Trial inclusion and exclusion criteria

The included patients will be required to be at least 18 years old and have a diagnosis of anxiety (F40.x, F41.x, according to ICD-10) [16] and/or depressive disorder (F32.x, F33.x, F34.1). The diagnoses will be validated with the Mini-DIPS diagnostic interview [17], which is a short version of the DIPS diagnostic interview for mental disorders [18]. Comorbid mental disorders or somatic comorbidity will not be an exclusion criterion.

Patients who are already in a concurrent outpatient psychotherapeutic treatment at admission that will be continued after the inpatient treatment will be excluded from the study because aftercare coordination will not be necessary for those patients. Further exclusion criteria include acute risk of suicide, acute psychosis or psychotic symptoms, insufficient German language skills and an inpatient treatment duration of less than three days.

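### The primary model's fixed covariates leave out diagnosis group, which is known before randomisation, cheap to add and plausibly prognostic for the BDI-II

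*Protocol*

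**What the plan says.** The Statistical analyses section of the protocol specifies a mixed-model ANCOVA comparing the two arms, with "symptom severity as the dependent variable and gender and initial symptom severity as covariates". The outcome is set under Primary outcome measures: "The primary outcome measure is symptom severity, which will be assessed using Beck's Depression Inventory (BDI-II"). It is used for every patient.

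Trial inclusion and exclusion criteria admits patients with an anxiety disorder "and/or depressive disorder (F32.x, F33.x, F34.1"), so the sample can hold three groups: depressive only, anxiety only, and both. The same section adds: "The diagnoses will be validated with the Mini-DIPS diagnostic interview". Eligibility is settled at the start of the inpatient stay, and randomisation takes place one week before the intervention begins, so diagnosis is a true baseline variable.

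Under Randomization, "the randomization will be stratified by the participating clinical units"; no other stratifier is given. The predictor regressions are to use "patient characteristics (e.g., age, level of education, and psychosocial treatment before the inpatient treatment"), and the fuller list under Additional measures does not name diagnosis either. On clinical course, the Background states: "Depressive disorders are particularly highly recurrent, and the risk of a further episode increases with each additional episode".

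**The concern.** A depression scale is the primary outcome in a sample that includes patients without a depressive diagnosis. Baseline BDI-II records severity at discharge. It need not capture liability to recurrence, so patients with equal discharge scores but different diagnoses may differ at 9 months. If they do, omitting diagnosis has three consequences:

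- Explainable variance stays in the error term.
- Chance imbalance in diagnosis between the arms is left unadjusted.
- With about half the patients expected to be lost by 9 months, the model does not condition on a factor that may relate to both outcome and retention. A likelihood-based mixed model is protected against informative loss only to the extent that loss is random given what the model contains.

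The covariate set is written into the protocol, so this is a stated choice and not a detail left open for a later plan.

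**Working it through.** **Inputs from the protocol (Power calculation).** Unadjusted f = 0.25 (d = 0.50); about 30% of error variance removed by baseline BDI-II; adjusted f = 0.29; power 80%; alpha 0.05 (taken as the usual F test); N = 96 evaluable, 48 per arm; about 50% drop-out; N = 192 enrolled.

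**Inputs assumed, because the protocol does not give them.** The extra share r of residual variance that diagnosis explains, 0 to 10%; the anxiety-only share p, 20 to 40%; the gap in 9-month BDI-II between anxiety-only and other patients at equal baseline BDI-II, 2 to 6 points; BDI-II SD, 10 to 12; and the pattern of loss by diagnosis.

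**1. The plan's own figure.** Noncentral F with 1 and N − 2 − c degrees of freedom (c = covariate degrees of freedom) and noncentrality f²N. At f = 0.29 and N = 96 the noncentrality is 0.0841 × 96 = 8.07 and power is 80.3%. N = 96 reproduces, and 96 / (1 − 0.5) = 192. A 30% reduction would strictly give 0.25/√0.70 = 0.299, so the stated 0.29 is slightly conservative.

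**2. Adding diagnosis group.** Gender and baseline BDI-II give c = 2; three diagnosis levels make it c = 4. The effect size becomes 0.29/√(1 − r). Without diagnosis, power at N = 96 is 80.28%.

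| r (assumed) | f | Power at N = 96 | Evaluable N for 80% | Standard error ratio |
|---|---|---|---|---|
| 0% | 0.2900 | 80.26% | 96 | 1.000 |
| 1% | 0.2915 | 80.65% | 95 | 0.995 |
| 2% | 0.2929 | 81.04% | 94 | 0.990 |
| 3% | 0.2945 | 81.44% | 93 | 0.985 |
| 5% | 0.2975 | 82.23% | 91 | 0.975 |
| 10% | 0.3057 | 84.21% | 87 | 0.949 |

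The cost when diagnosis is useless is 0.02 power points. The gain at r = 10% is 84.21 − 80.28 = 3.9 points.

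**3. What r might be.** For anxiety-only against the rest, r = p(1 − p) × gap² / (0.7 × SD²).

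- Low: 0.16 × 4 / (0.7 × 144) = 0.6%.
- Middle (p = 0.3, gap 4, SD 11): 0.21 × 16 / (0.7 × 121) = 4.0%.
- High: 0.24 × 36 / (0.7 × 100) = 12.3%.

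The high corner needs all three extremes at once, with a gap as large as the planned treatment effect (0.5 × 10 to 12 = 5 to 6 points). A gap of zero, giving r = 0, is also possible.

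**4. Chance imbalance.** At p = 0.3 and 48 completers per arm, the between-arm difference in the anxiety-only share has SD √(2 × 0.3 × 0.7 / 48) = 9.4 percentage points. A 1-in-20 imbalance (about 18 points) with a 4-point gap moves the contrast by about 0.7 BDI-II points.

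**5. Loss related to diagnosis and arm.** Suppose that in the control arm 65% of anxiety-only and 45% of other patients are lost, and that in the intervention arm 50% of each are lost. The anxiety-only share among completers is then 0.3 × 0.5 / (0.3 × 0.5 + 0.7 × 0.5) = 30.0% in the intervention arm, against 0.3 × 0.35 / (0.3 × 0.35 + 0.7 × 0.55) = 21.4% in the control arm. The difference of 0.086 times a gap of 2 to 6 points gives 0.17 to 0.51 points. The standard error of the contrast is √0.7 × SD × √(2/48) = 1.7 to 2.0 points for SD 10 to 12, so this is about 0.1 to 0.3 standard errors. The figure is for a completers-only comparison.

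**The case against.** The case against is substantial, and several stronger readings that a reader might infer do not stand.

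- *That the protocol itself says diagnosis drives the course after discharge.* It does not. The Background calls depressive disorders highly recurrent and ties risk to the number of earlier episodes, which diagnosis group does not record. It does not compare the three groups and says nothing about 9-month BDI-II at equal discharge scores. Prognostic value is plausible, not documented.
- *That no analysis uses diagnosis.* Diagnosis decides who receives the disorder-specific anxiety scales, and the fourth objective concerns patients with different anxiety disorders. The predictor list is introduced as examples, and the drop-out comparison of clinical baseline characteristics could include diagnosis. What can be said is that neither the primary nor the predictor analysis names it.
- *That the model cannot absorb imbalance or loss.* Baseline BDI-II absorbs part of both, and observed 3-month BDI-II part of the loss. Chance imbalance under randomisation is not bias and is already reflected in the standard error. The loss scenario needs dropout to depend on diagnosis differently in the two arms, and nothing in the protocol suggests that it will.
- *That the joint conclusion requires subgroup estimates.* The protocol deliberately defines a joint population. At an assumed 30% anxiety-only share there would be about 0.3 × 48 ≈ 14 such completers per arm. The 95% interval would be about 1.96 × √0.7 × SD × √(2/14), or ±6 to 7 points, which is wider than the planned effect of 5 to 6. Such a display could not show that effects are alike, and it is the kind of detail often left to a statistical analysis plan.

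Adjusting for gender without a stated reason is not an error either. None of this supplies a reason to leave diagnosis out of the primary model.

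**Conclusion.** The point holds as a recommendation on the covariate set. The protocol fixes a primary model that omits a baseline variable which is already collected, validated by interview and plausibly related to the outcome, when including it costs practically nothing. The benefit is uncertain: roughly 0 to 4 power points, depending on an assumed 0 to 10% of residual variance, and it may be small because baseline BDI-II overlaps with diagnosis. Some further protection against loss related to diagnosis is possible, but its size cannot be established from the protocol. The protocol contains no wrong figure or contradiction here; N = 96 evaluable and N = 192 enrolled both reproduce. The finding does not show that the planned analysis is biased.

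**What to change.** In Statistical analyses, extend the primary covariates to: gender, initial symptom severity, and diagnosis group (depressive disorder only / anxiety disorder only / both, from the entry diagnosis). In the same section, name diagnosis group among the predictors and in the comparison of completers with non-completers, and add it to the characteristics listed under Additional measures.

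The cost is a line or two of wording and two degrees of freedom. No new data, visits or patients are needed, and N = 192 is unchanged. The change should be made before outcome data are seen, because a covariate added later would look selected. A display of the arm difference by diagnosis group is optional; if given, it should be labelled descriptive and imprecise.
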